## Abstract

**Background:**

To improve the performance of health care institutions, reduce overmedication, and minimize the waste of medical resources, China is committed to implementing a clinical pathway management model. This study aims to standardize nursing practices, foster clinical thinking in nurses, and promote patient recovery.

**Objective:**

The purpose of this study is to evaluate the clinical effects of a traditional Chinese medicine (TCM) nursing program based on nursing pathways for patients with type 2 diabetes mellitus (T2DM).

**Methods:**

This study uses a prospective, randomized, single-blind, parallel-controlled design. Based on sample size calculations, the study will include 594 patients with diabetes, with 2 groups of 297 patients: an observation group will receive a TCM nursing program based on clinical pathways, while a control group will receive routine care. Both groups will be evaluated before and after the intervention using assessment indicators. The primary outcome is the quality of life score, measured by a diabetes-specific quality of life questionnaire. Secondary outcomes include hospital stay duration, medical expenses, health knowledge, blood glucose control, symptom scores, and patient satisfaction.

**Results:**

This study was funded in August 2021 and has received approval from the Ethics Committee of Guang’anmen Hospital, China Academy of Chinese Medical Sciences (2022-022-KY-01). The trial is ongoing, with the first patient enrolled in September 2022. The study is expected to conclude in April 2025. To date, 380 patients have been recruited, with 202 randomized into the study, though no statistical analysis of the data has yet been conducted. A single-blind method is used; nurses are aware of group assignments and intervention plans, while patients remain blinded. Final results are planned for release in the first quarter of 2025.

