## Methods

### Study Design

The intervention protocol for this study is titled “TCM Nursing Protocol for Type 2 Diabetes Based on Care Pathway.” The study uses a prospective, randomized, single-blind, parallel-controlled clinical design and aims to assess and demonstrate differences, supported by high-quality evidence, in outcomes between an intervention group and a control group that received standard care. The research team comprises nurses from the Department of Endocrinology at Guang’anmen Hospital, China Academy of Chinese Medical Sciences. The study participants are patients with T2DM admitted to our department between September 2022 and December 2024. The study is registered with the International Traditional Medicine Clinical Trial Registry (ITMCTR2022000048). Inclusion, exclusion, and elimination criteria are shown in Textbox 1.

Inclusion, exclusion, and elimination criteria.

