**Elimination criteria**
Patients whose condition worsens, resulting in a hospitalization duration exceeding 14 days and increased hospitalization costs.Patients with concomitant systemic diseases that require special treatment, leading to a hospitalization duration exceeding 14 days and increased costs.Patients with serious complications that arise during the course of treatment and necessitate discontinuation of the nursing pathway.Patient and family preferences and wishes that affect the implementation of this nursing pathway.

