#### Outcomes

Researchers use standardized questionnaires to collect baseline data. The primary efficacy indicator is a quality of life scale (the Diabetes-Specific Quality of Life Scale) [11]. Secondary efficacy indicators include the length of hospital stay, medical costs, blood glucose control, patient symptom scores, patient satisfaction, and the level of health knowledge acquired at admission. Data are collected 1 day before discharge and at 4 weeks, 12 weeks, and 24 weeks after discharge.

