## Results

This trial received funding in August 2021 and is currently ongoing. The first patient was enrolled in September 2022, and the study is expected to conclude in December 2024. The trial uses a single-blind design where nurses are aware of group assignments and intervention details, but the patients remain blinded. Final results are planned for publication in the first quarter of 2025.

To date, 380 patients have been recruited, with 172 excluded, resulting in 202 randomized participants (101 in the study group and 101 in the control group). Details on the screening process are provided as a Consolidated Standards of Reporting Trials (CONSORT) flowchart in Multimedia Appendix 2.

This study primarily aims to compare health knowledge, comprehension, and scores between the 2 groups, with the goal of optimizing an innovative model for the TCM nursing pathway for T2DM. The findings are expected to enhance the standardization and precision of clinical nursing practices. The pathway will be validated clinically, combining theory with practice through prospective research to provide high-level clinical evidence. This will contribute to the development of a high-quality TCM nursing pathway, expand the global influence of TCM, and support national economic growth and public health.

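### The end and release dates conflict with each other, and all of them fall before the 24-week follow-up could be complete

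*Protocol article*

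**What the plan says.** Five statements in the protocol article fix the calendar.

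- **Admission window** (Methods, Study Design): "The study participants are patients with T2DM admitted to our department between September 2022 and December 2024".
- **Follow-up** (Methods, Outcomes): "Data are collected 1 day before discharge and at 4 weeks, 12 weeks, and 24 weeks after discharge".
- **Study end, Abstract (Results paragraph):** "The study is expected to conclude in April 2025".
- **Study end, main Results section:** "the study is expected to conclude in December 2024".
- **Final results:** "Final results are planned for release in the first quarter of 2025" in the Abstract and "Final results are planned for publication in the first quarter of 2025" in the main Results section.

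The only figure that bears on length of stay is in the elimination criteria, where worsening or a systemic disease leading to more than 14 days in hospital is a ground for removal ("resulting in a hospitalization duration exceeding 14 days and increased hospitalization costs").

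**The concern.** There are three conflicts. The two end dates differ by about four months. Under the Abstract's own dates, the final results come out before the study has ended. And a patient admitted at the close of the window cannot reach the week-24 assessment by either end date or by the release date.

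If the calendar were followed literally, the final comparison would be made on incomplete follow-up. The missing assessments would all belong to the most recently enrolled patients, because the calendar and not the patient decides who is missing. The week-24 comparison would rest on fewer patients than planned. Quality of life is the primary outcome and week 24 is one of its possible collection points. The article's aims for self-care and medication adherence after discharge also depend on post-discharge data.

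**Working it through.** **Inputs.** Admission window: 1 September 2022 to 31 December 2024, taking whole months, which is 852 days from first to last date (Study Design). Last visit: 24 weeks = 168 days after discharge (Outcomes). Week-12 visit: 84 days after discharge. End dates: December 2024 (main Results) and April 2025 (Abstract). Release: first quarter of 2025 (both). Each period is taken at its last day, which favours the plan. Length of stay: 0 to 14 days, an assumption, since the 14-day figure in the elimination criteria is tied to particular causes and is not a general cap. Planned size: 594 (Abstract, Methods).

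The article gives no derivation of its end dates, so there is no calculation to reproduce. The check is whether any stated date can be reached from the window and the visit schedule.

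**Step 1. Date of the last week-24 visit** = admission + stay + 168 days.

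| Last admission | 0-day stay | 14-day stay |
|---|---|---|
| 1 December 2024 | 18 May 2025 | 1 June 2025 |
| 31 December 2024 | 17 June 2025 | 1 July 2025 |

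The most favourable cell, 18 May 2025, is 18 days after 30 April 2025, the latest stated date. The least favourable, 1 July 2025, is 62 days after it.

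**Step 2. Latest discharge that still allows a week-24 visit** = stated date − 168 days. The uncovered tail is the number of days from that discharge date to 31 December 2024. The share is tail / 852, assuming even accrual and treating discharge as the day of admission. With a 14-day stay, 14 days are added to the tail.

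| Stated date | Latest discharge | Tail, 0-day stay | Share; patients of 594 | Tail, 14-day stay | Share; patients of 594 |
|---|---|---|---|---|---|
| 31 December 2024 (end) | 16 July 2024 | 168 days | 19.7%; 117 | 182 days | 21.4%; 127 |
| 31 March 2025 (release) | 14 October 2024 | 78 days | 9.2%; 54 | 92 days | 10.8%; 64 |
| 30 April 2025 (end) | 13 November 2024 | 48 days | 5.6%; 33 | 62 days | 7.3%; 43 |

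**Step 3. The same for week 12** = stated date − 84 days.

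- End 31 December 2024: latest discharge 8 October 2024. The tail is 84 days, and 84 / 852 = 9.9%.
- Release 31 March 2025: latest discharge 6 January 2025. Nobody is lost with a 0-day stay. With a 14-day stay, admissions after 23 December 2024 are lost, a tail of 8 days, and 8 / 852 = 0.9%.
- End 30 April 2025: 31 December 2024 + 14 + 84 days = 8 April 2025, so nobody is lost.

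Week-12 loss is therefore material only under the December 2024 end.

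**Step 4. Order of the Abstract's dates.** The first quarter closes on 31 March 2025 and April opens the day after. Release precedes the end of the study on any reading of the two.

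**The case against.** The dates are worded as expectations and plans. None is a data-cut or database-lock rule, and nothing says that visits stop on a calendar date. The operative instruction is the visit schedule, which runs to 24 weeks. This stands, and it limits the weight of the point: the likely consequence is a late report. It does not remove the point, because an author or reader who relies on the printed dates would expect final results before follow-up is complete.

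December 2024 in the main Results section could be meant as the end of enrolment. That would explain one of the two end dates. April 2025 and the first-quarter release would still be too early.

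Recruitment might close before December 2024. The article does not say so, and Study Design gives December 2024 as the close of the admission window.

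Two stronger readings are tempting and are not supported.

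- **That the primary result is compromised.** The article names no primary time point. It describes evaluation before and after the intervention and includes a collection one day before discharge. If that is the primary assessment, quality of life is untouched by the late cut-off, and so are length of stay and in-hospital costs.
- **That the trial will close well short of 594 and lose its power.** A reader might infer this from "To date, 380 patients have been recruited, with 202 randomized into the study". The count carries no date, so it gives no accrual rate, and nowhere does the article say that enrolment will stop at that number or on a date below the target. How a shortfall would be handled is a matter that an article may leave to the full protocol.

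**Conclusion.** The point holds as an internal contradiction in the timetable. It rests on printed dates and not on missing detail, and it survives the reading most favourable to the plan. The existence of the conflict does not depend on the assumed length of stay.

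The share of patients without week-24 data, about 6% to 20% depending on which stated date governs, does rest on even accrual over the whole window. If enrolment is weighted towards the end the share is larger, and if towards the start it is smaller. A stay of 14 days rather than 0 adds under two percentage points. Whether the primary analysis or only a later assessment is affected cannot be decided from the article.

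This should be fixed, but as a correction of forecast dates it does not call the design into question.

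**What to change.** Give one timetable in the Abstract (Results paragraph), Methods (Study Design) and the main Results section. There are two ways to do this.

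1. **Keep the admission window.** Define the end of the study as the last discharge plus 24 weeks, about 1 July 2025 if admissions run to 31 December 2024 and the last stay is 14 days. State that database lock, the final comparative analysis and release follow that date.
2. **Keep an end date and close admissions earlier.** For an end on 30 April 2025 with a stay of up to 14 days, the last admission would be 30 April 2025 − 168 − 14 days = 30 October 2024. The release must still move to after the end of the study.

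The first option costs a release some months later. The second gives up about two months of recruitment (62 of 852 days). Neither needs extra patients or procedures.

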**Conclusions:**

This study seeks to integrate existing national standardized nursing protocols with clinical pathways to implement more efficient and higher-quality nursing practices. The goal is to standardize nursing procedures, enhance patients’ quality of life, and improve self-care and medication adherence after discharge.

**Trial Registration:**

International Traditional Medicine Clinical Trial Registry ITMCTR2022000048; https://tinyurl.com/y4jd68h4

**International Registered Report Identifier (IRRID):**

DERR1-10.2196/58951

## Introduction

According to the Guideline for the Prevention and Treatment of Type 2 Diabetes Mellitus in China (2020 Edition) [1], the prevalence of diabetes in China has surged from 0.67% in 1980 to 11.2% in 2015-2017 [2,3]. Diabetes management in China faces significant challenges, particularly in rural areas where awareness, treatment, and control rates remain low. Large-scale epidemiological surveys conducted in 2010 and 2013 reported diabetes awareness rates of 30.1% and 36.5%, treatment rates of 25.8% and 32.2%, and control rates of 39.7% and 49.2%, respectively [3-5].

Most existing studies have focused on evaluating clinical nursing pathways or nursing programs. For instance, a study by Li [6] analyzed the effectiveness of clinical nursing pathways in type 2 diabetes mellitus (T2DM) care, demonstrating that a research group using clinical nursing pathways achieved better control of fasting blood glucose and postprandial 2-hour glucose levels compared to a control group (*P*<.05). The research group also had significantly fewer instances of improper hypoglycemia treatment, insulin injection errors, dietary mistakes, inadequate exercise, and nonadherence to medical advice (*P*<.05). Additionally, compared to the control group, the research group had shorter hospital stays, lower hospitalization costs, and higher overall nursing satisfaction (*P*<.05), indicating that the application of clinical nursing pathways can effectively control blood glucose levels, improve nursing quality, and enhance patient satisfaction.

Similarly, a study by Ren et al [7] showed that implementing traditional Chinese medicine (TCM) nursing programs in general hospitals resulted in higher quality-of-life scores for patients in an observation group 1 month after discharge compared to a control group. At discharge, the observation group had a significantly higher nursing satisfaction rate (93%) than the control group (77%; *P*<.05). This suggests that the TCM nursing program model can improve both quality of life and nursing satisfaction. These studies demonstrate that clinical nursing pathways or TCM nursing programs can effectively control blood glucose levels and reduce medical costs while enhancing patients’ quality of life. However, no studies to date have explored the combined clinical application of these two nursing methods, which is the focus of our study.

The evolution of national standards and their integration with nursing practices have increasingly shifted the focus toward nursing pathways aligned with these standards. This development combines nationally standardized nursing protocols with nursing pathways to create a coherent, interconnected, and progressive nursing model. Pathway-based TCM nursing interventions built on TCM clinical pathways standardize the care of single diseases, promote systematic intervention processes, highlight the efficacy and unique features of TCM, and make nursing operations more standardized. This enables nurses to provide planned and anticipatory care based on structured procedures. A preliminary retrospective analysis of clinical data from 4196 patients with diabetes revealed that integrating traditional Chinese nursing techniques with clinical treatments effectively alleviated patients’ discomfort. Nurses found this approach more practical and valuable in standardizing care, reducing variability, lowering costs, and improving care quality for patients with T2DM [8,9]. Nevertheless, no research has yet examined the simultaneous clinical application of these two nursing methods, which is the aim of our study.

Thus, we conducted a prospective, randomized, single-blind, parallel-controlled trial to further investigate the impact on patient outcomes of integrating nationally standardized nursing protocols with TCM nursing programs based on clinical pathways. These outcomes include hospitalization indicators (eg, length of stay and medical costs), self-management (health knowledge), clinical efficacy (blood glucose control, clinical symptoms, and quality of life), and patient satisfaction. We expect that the findings of this study will provide robust evidence for delivering personalized care, standardizing procedures, improving patients’ quality of life, and enhancing self-care and medication adherence after discharge.

## Methods

### Study Design

The intervention protocol for this study is titled “TCM Nursing Protocol for Type 2 Diabetes Based on Care Pathway.” The study uses a prospective, randomized, single-blind, parallel-controlled clinical design and aims to assess and demonstrate differences, supported by high-quality evidence, in outcomes between an intervention group and a control group that received standard care. The research team comprises nurses from the Department of Endocrinology at Guang’anmen Hospital, China Academy of Chinese Medical Sciences. The study participants are patients with T2DM admitted to our department between September 2022 and December 2024. The study is registered with the International Traditional Medicine Clinical Trial Registry (ITMCTR2022000048). Inclusion, exclusion, and elimination criteria are shown in Textbox 1.

Inclusion, exclusion, and elimination criteria.
**Inclusion criteria**
The primary diagnosis must align with *International Classification of Diseases, Tenth Revision* codes for type 2 diabetes mellitus, specifically in the range of E11.2 to E11.9.Admission criteria must be met for inpatient treatment, as determined by the clinical physician.In cases where patients have concurrent diagnoses of other diseases, if these conditions do not require special treatment during the hospital stay and do not hinder the implementation of the clinical nursing pathway for the primary diagnosis, the patient can be included in that nursing pathway.Informed consent must be obtained from the patient and documented, indicating their understanding and agreement with the proposed care plan.
**Exclusion criteria**
Patients who meet the diagnostic criteria for type 2 diabetes mellitus but are unable to comply with the treatment regimen.Patients with cognitive impairments or cognitive dysfunction.Patients with concurrent diagnoses of other diseases that require treatment during the hospitalization period.
**Elimination criteria**
Patients whose condition worsens, resulting in a hospitalization duration exceeding 14 days and increased hospitalization costs.Patients with concomitant systemic diseases that require special treatment, leading to a hospitalization duration exceeding 14 days and increased costs.Patients with serious complications that arise during the course of treatment and necessitate discontinuation of the nursing pathway.Patient and family preferences and wishes that affect the implementation of this nursing pathway.

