### Interventions

#### Intervention Plan

Upon admission, nurses provide admission education and assign eligible patients to the study group or the control group based on the time of admission (Figure 1). The intervention plans for both groups are outlined in a pathway form and include 3 components: executing medical orders, nursing tasks, and health education, along with TCM-specific treatments (Multimedia Appendix 1). For the control group, nurses subjectively implement the nursing plan according to the pathway form. The study group strictly follows the TCM nursing pathway for T2DM.

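### The elimination criteria act after allocation and, in their ordinary sense, select patients on length of stay and cost (two secondary outcomes) and on prognosis

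*Protocol article*

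**What the plan says.** The protocol article (Methods, Textbox 1) has three lists: inclusion, exclusion and elimination. The elimination list has four entries:

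1. "Patients whose condition worsens, resulting in a hospitalization duration exceeding 14 days and increased hospitalization costs"
2. "Patients with concomitant systemic diseases that require special treatment, leading to a hospitalization duration exceeding 14 days and increased costs"
3. "Patients with serious complications that arise during the course of treatment and necessitate discontinuation of the nursing pathway"
4. "Patient and family preferences and wishes that affect the implementation of this nursing pathway"

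On timing, the Intervention Plan section says: "Upon admission, nurses provide admission education and assign eligible patients to the study group or the control group based on the time of admission". On endpoints, the Outcomes section says: "Secondary efficacy indicators include the length of hospital stay, medical costs, blood glucose control, patient symptom scores, patient satisfaction". The primary outcome is the diabetes-specific quality-of-life scale, and data collection runs to 24 weeks after discharge.

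On the arms, the Intervention Plan section says "The study group strictly follows the TCM nursing pathway for T2DM". Control nurses implement their plan at their own judgement, also from a pathway form. The Abstract and the Results section say that nurses know the allocation. The Statistical Analysis section names tests but does not say how eliminated patients are handled.

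**The concern.** A separate elimination list implies something other than screening, and its triggers fit that reading. A stay over 14 days, the cost of that stay and a complication during treatment cannot be known when the patient is allocated. A preference that affects how the pathway is carried out will usually show itself after allocation too.

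Three things are at stake.

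- **Selection on outcomes.** Criteria 1 and 2 require a long stay and raised costs. Both are secondary outcomes, so the comparison of stay and cost would be made among patients chosen partly by their stay and cost.
- **Selection on prognosis.** Criteria 1 and 3 pick out patients who worsen or have serious complications. Such patients plausibly score worse on quality of life, so the primary comparison is exposed as well.
- **Possibly unequal action.** Criteria 3 and 4 are worded around the pathway, which only the study group must follow strictly, and the nurses who deliver and check the care are unblinded. Judging whether a preference affects implementation leaves room for discretion.

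**Working it through.** **Timing and overlap, from the text.**

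| Criterion | Trigger | Known at allocation? | Tied to |
|---|---|---|---|
| 1 | Worsening that leads to a stay over 14 days and raised cost | No | Stay, cost, prognosis |
| 2 | Systemic disease that leads to a stay over 14 days and raised cost | Disease perhaps; stay and cost no | Stay, cost |
| 3 | Serious complication that ends the pathway | No | Prognosis, pathway |
| 4 | Preferences that affect the pathway | Usually not | Acceptance of the pathway |

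**Size.** The article has no figure to reproduce here: it gives no stay distribution and no elimination rate. All inputs below are assumptions, apart from the 14-day limit.

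- Stay is lognormal with log-SD s = 0.3; median m = 12 days (control) and 11 days (study).
- A fraction f of stays over 14 days is eliminated at random. f = 1 is the upper bound, because criteria 1 and 2 also require worsening or systemic disease.
- Quality of life is normal with SD 1, a true difference of 0.20 SD, and correlation r with log stay within each arm.

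Formulas:

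- b = ln(14/m)/s: 0.514 (control), 0.804 (study).
- Share over 14 days, P = 1 − Φ(b): 0.304 and 0.211.
- Full mean, M = m·exp(s²/2): 12.55 and 11.51 days. True difference 1.05 days.
- Part of the mean from stays over 14 days, L = M·Φ(s − b): 5.21 and 3.53.
- Mean among those kept = (M − f·L)/(1 − f·P).
- Mean standardized log stay among those kept, k = −f·φ(b)/(1 − f·P).
- Retained quality-of-life difference = 0.20 + r·(k for study − k for control).

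With f = 1, the control mean is (12.55 − 5.21)/0.696 = 10.54 and the study mean is (11.51 − 3.53)/0.789 = 10.10, a difference of 0.44 days. The values of k are −0.502 (control) and −0.366 (study), which differ by 0.136. The quality-of-life difference is 0.20 − 0.3 × 0.136 = 0.16 SD, or 0.20 − 0.5 × 0.136 = 0.13 SD.

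| Fraction f eliminated | Removed, control vs study | Stay difference (true 1.05 days) | Quality of life, r = −0.3 (true 0.20 SD) | Quality of life, r = −0.5 |
|---|---|---|---|---|
| 1 (upper bound) | 30% vs 21% | 0.44 | 0.16 | 0.13 |
| 0.5 | 15% vs 11% | 0.84 | 0.19 | 0.18 |
| 0.25 | 8% vs 5% | 0.96 | 0.19 | 0.19 |
| 0.1 | 3% vs 2% | 1.01 | 0.20 | 0.20 |

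Other assumptions give a similar upper bound. Lognormal medians of 11 and 10 days remove 21% vs 13% and leave 0.54 of 1.05 days. Normal stays with means 12 and 11 and SD 3 remove 25% vs 16% and leave 0.58 of 1.0 day.

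This models only criteria 1 and 2, where the loss shrinks a true benefit. Criteria 3 and 4 could work the other way if they take patients with a poor course mainly out of the study group. The article offers nothing from which to size that.

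**The case against.** The best defence is that the article does not define elimination and nowhere says that eliminated patients leave follow-up or analysis. Analysis sets are commonly left to the full protocol or the SAP, neither of which is shown. That stands as a limit on certainty: removal is the ordinary meaning of the word, not a stated fact. It does not dispose of the point, because the article does state the rule and nothing in it limits the rule's effect.

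Several stronger readings are tempting, and the text does not support them.

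- **Every stay over 14 days is eliminated.** The long stay must follow from worsening or from systemic disease. Criterion 2 may also partly catch patients who should have been excluded at entry, although it still conditions on stay and cost.
- **Non-adherent patients are eliminated.** Criterion 4 speaks of preferences that affect implementation, and may partly describe withdrawal, which Ethical Considerations allows at any time.
- **The criteria act mainly in the study arm.** None is limited to one arm, both plans sit on a pathway form, and the head nurse checks both daily. Nor does the article say who decides on elimination. Unequal action is possible, not established.
- **The primary comparison is certainly distorted.** If few long stays meet the criteria, the modelled effect on quality of life is close to nil, as the last rows of the table show.
- **Randomized patients have already been dropped.** The article reports none; Results places its 172 exclusions before randomization.

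**Conclusion.** The concern holds as a fault in a stated rule. The criteria operate after allocation; two of the four condition on length of stay and cost, and criteria 1 and 3 condition on a poor clinical course. Read in the ordinary sense, they undo part of what randomization secures, for two secondary outcomes and potentially for the primary.

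The size is unknown. Under the main assumed stay model, a 1.05-day difference is retained as anything from 0.44 days (all long stays eliminated) to 1.01 days (a tenth eliminated). A 0.20 SD quality-of-life effect is retained as 0.13 to 0.20 SD. These figures cover attenuation only. Differential use of criteria 3 and 4 could push in favour of the study group, so the rule cannot be defended as merely conservative. It should be corrected before analysis; the article reports that no statistical analysis has yet been done.

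**What to change.** State in the protocol and the SAP that:

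- the elimination criteria do not remove a patient from follow-up or from the primary analysis;
- all randomized patients are analysed in the group assigned, with stays over 14 days and their full costs included;
- outcomes are collected to 24 weeks after discharge unless consent is withdrawn;
- the elimination criteria serve only to define a per-protocol set, labelled as a sensitivity analysis;
- the number of patients meeting each criterion is reported by arm and reason;
- any randomized patient already eliminated is included where data are available.

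This changes follow-up and analysis only. It does not recast the criteria as reasons for stopping the pathway, which criteria 1 and 2 do not say, and it sets no clinical rule. The cost is a change of wording, some extra follow-up, and an estimate that may be less favourable.
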